##### 2.6.1.3 ​​Quality of life (QL) evaluation​​

QL was assessed using validated tools:① COPD Assessment Test (CAT)​​: An eight-item questionnaire scoring symptoms (cough, dyspnea) and functional limitations (0–40 scale). A 5-point change indicates clinically meaningful improvement.② mMRC Dyspnea Scale​​: Grades breathlessness from 0 (no dyspnea) to 4 (dyspnea at rest). Scores ≥2 correlate with increased hospitalization risk.③ Baseline Dyspnea Index (BDI)​​ and ​​Transition Dyspnea Index (TDI)​​: BDI assesses dyspnea impact on daily activities (e.g., task difficulty), while TDI measures changes post-treatment. A TDI score ≥1 signifies meaningful improvement.​​④ Chest Radiography​​: Screened for structural abnormalities (e.g., hyperinflation, effusions) but limited in detecting early small airway disease.​​⑤ High-Resolution CT (HRCT)​​: Quantified emphysema extent, airway wall thickness, and fibrosis patterns. Dynamic CT evaluated ventilation-perfusion mismatches in advanced cases.⑥ Acute Exacerbation of COPD (AECOPD): Exacerbation Frequency Classification: Based on events in the previous 12 months. Infrequent exacerbators: ≤1 exacerbation/year without hospitalization; Frequent exacerbators: ≥2 exacerbations/year or ≥1 requiring hospitalization.

#### 2.6.2 Secondary outcomes

Secondary outcomes will include TCM syndrome differentiation scoring, implemented per the Guidelines for Clinical Research of New Chinese Medicines (Trial). Symptomatology is categorized as follows: Core symptoms: Graded 0 (absent), 2 (mild), 4 (moderate), 6 (severe); Ancillary symptoms: Graded 0 (absent), 1 (mild), 2 (moderate), 3 (severe); Non-scored elements: Tongue manifestation and pulse characteristics. The composite TCM syndrome score is calculated through summation of all graded symptom scores.

#### 2.6.3 Safety assessment and adverse events reporting

An independent Data Safety Monitoring Board (DSMB)—comprising a pulmonologist, a clinical pharmacologist, and a biostatistician with no study roles—will oversee participant safety. The DSMB will review aggregate safety data at predefined intervals and *ad hoc* as needed, operating under a written charter with prespecified review procedures, communication pathways, emergency unblinding procedures, and stopping rules.

Safety surveillance will involve serial biochemical monitoring during pre-treatment, on-treatment, and post-treatment phases to establish the safety profile of Yiqi Gubiao Pill. All adverse events occurring during the study period will be prospectively monitored and systematically documented. Participants will be instructed to self-report potential adverse events in real-time, and researchers will determine whether the event is related to the study medication. If the adverse event is related to the study formulation, it is then referred to as a side effect. If the side effects are mild and the patient agrees to continue the treatment, medication will be continued after the symptoms have subsided. In case of serious adverse events due to the trial medication, the researcher will report to the DSMB and research ethics committee within 24 h, ask the patient to discontinue the medication, and implement emergency safety measures.

### 2.7 Data collection and management

Data collection will be carried out before, during, and after treatment (Table 2). Data will be recorded on pre-designed case report forms (CRF) and transferred to an electronic format (RevMan 5.3) for storage and data backup. All patient identity information will be encoded.

**TABLE 2 T2:** Participant enrollment process, interventions, and outcome measures.

Items	Baseline	Treatment phase (monitor monthly)			Follow-up phase (monitor monthly)		
		1 month	2 months	3 months	3 months	6 months	12 months
Enrolment							
Recruitment	●						
Eligibility Screening	●						
Signed written informed consent	●						
Allocation	●						
Intervention							
Yiqi Gubiao pill (Treatment group)		●	●	●	●	●	●
Yiqi Gubiao pill Placebo (Control Group)		●	●	●	●	●	●
Outcomes							
forced vital capacity (FVC)	●	●	●	●	●	●	●
the percentage of FVC predicted (FVC%)	●	●	●	●	●	●	●
the percentage of forced expiratory volume in one second predicted (FEV1%)	●	●	●	●	●	●	●
FEV1/FVC	●	●	●	●	●	●	●
CAT score	●	●	●	●	●	●	●
mMRC score	●	●	●	●	●	●	●
BDI score	●	●	●	●	●	●	●
TDI score	●	●	●	●	●	●	●
chest X-ray/CT	●	●	●	●	●	●	●
Traditional Chinese Medicine Symptom (TCMS) score	●	●	●	●	●	●	●
Security							
All adverse events (including symptoms, signs, etc.)		●	●	●	●	●	●
Liver function: alanine aminotransferase, aspartate aminotransferase, total bilirubin, albumin, globulin	●	●	●	●	●	●	●
Renal function: uric acid, urea nitrogen, serum creatinine, β2-microglobulin, urinary protein, carbon dioxide binding rate, cystatin C	●	●	●	●	●	●	●

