**Methods:**

We will implement a prospective double-blind randomized controlled trial utilizing 1:1 allocation ratio, randomly assigned to either the Yiqi Gubiao pill treatment group or placebo-controlled group. Following randomization, a standardized 12-week therapeutic protocol will be administered, during which serial pulmonary function assessments and quality of life evaluations will be conducted. Concurrently, validated Traditional Chinese Medicine (TCM) symptom scoring scales will be applied for score. Systematic safety surveillance will be performed through weekly monitoring of adverse events.

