## 2 Methods and analysis

### 2.1 Study design

This prospective double-blind randomized controlled trial, registered with the Clinical Trials (registration number: NCT06676800), will implement a 1:1 allocation design randomized to either the Yiqi Gubiao treatment group or placebo-controlled group. Following randomization, a 12-week therapeutic protocol will be administered, during which serial pulmonary function assessments and quality of life evaluations. TCM syndrome differentiation will be quantified through the validated TCM Symptom Score Scale, while safety surveillance will systematically monitor adverse events. The trial adheres to SPIRIT guidelines (Standard Protocol Items: Recommendations for Interventional Trials), with the completed checklist provided in Supplementary Material 1. The complete study workflow is detailed in Figure 1.

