### 2.5 Intervention

#### 2.5.1 Composition, preparation, and administration of the trial medication

The treatment group received Yiqi Gubiao Pill (specific composition detailed in Table 1; each pill containing 0.19 g, prepared by the Department of TCM Preparation, Affiliated Hospital of Traditional Chinese Medicine, Xinjiang Medical University). Administration consisted of 10 pills orally three times daily after meals, continued for 12 weeks. The control group received a placebo matching Yiqi Gubiao Pill in appearance and core color (primary ingredients: starch and caramel; prepared by the TCM Preparation Room, Affiliated Traditional Chinese Medicine Hospital of Xinjiang Medical University). Participants were instructed to take 10 placebo pills orally three times daily after meals for 12 weeks (Figure 2).

**TABLE 1 T1:** The composition of Yiqi Gubiao Pill.

Chinese name	Latin name	Medicinal site
Dang-shen	Codonopsis radix	Root
Fu-xiao-mai	*Triticum aestivum*	Fruit
Bai-zhu	Atractylodes macrocephala Koidz	Rhizome
Ban-xia	Pinelliae rhizoma	Tuber
Chen-pi	Citri reticulatae pericarpium	Pericarp
Zi-su-zi	Perillae fructus	Fruit
Fu-ling	Poria cocos	Sclerotium
Yi-yi-ren	Coicis semen	Fruit
Fang-feng	Saposhnikoviae radix	Root
Kuan-dong-hua	Farfarae flos	Flower bud
Bei-mu	Fritillariae pallidiflorae bulbus	Bulblet
Huang-qin	Scutellariae radix	Root
Pi-pa-ye	Eriobotryae folium	Leafage

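### Table 2 marks the study pill and placebo at the 3-, 6- and 12-month follow-up visits, contradicting the 12-week treatment stated everywhere in the text

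*Protocol article*

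**What the plan says.** The text is uniform on duration. The abstract states that "a standardized 12-week therapeutic protocol will be administered", and section 2.1 repeats it: "Following randomization, a 12-week therapeutic protocol will be administered". Section 2.5.1 says of the active arm: "Administration consisted of 10 pills orally three times daily after meals, continued for 12 weeks". Of the control arm it says: "Participants were instructed to take 10 placebo pills orally three times daily after meals for 12 weeks".

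Two further places presuppose a period after treatment. Section 2.6.3 plans biochemical monitoring before, on and after treatment. The sentence that introduces Table 2 in section 2.7 says that data are collected before, during and after treatment.

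Table 2 has a baseline column, a treatment phase (months 1, 2, 3) and a block headed "Follow-up phase (monitor monthly") with columns at 3, 6 and 12 months. The rows "Yiqi Gubiao pill (Treatment group") and "Yiqi Gubiao pill Placebo (Control Group") are marked in all three treatment columns and in all three follow-up columns.

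Section 2.6.1 makes long-term lung function decline a primary endpoint. Section 2.6.1.2 analyses it in patients with at least three valid tests over 12 months, and so relies on the follow-up visits.

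**The concern.** A visit schedule is an operative part of a protocol: it shows what is given and measured at each visit. Here it shows study medication at visits that, according to the text, come after treatment has ended.

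Two things depend on the answer. The first is how much study medication a participant receives, and hence what exposure the safety data describe. The second is what the 12-month decline endpoint estimates. Under the text, it compares a 12-week course plus whatever persists after it. Under the table read literally, it compares a year or more of continued treatment. These are different treatment effects, and section 2.6.1.2 does not say which is meant.

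The undefined time origin adds to this. A 3-month column appears in both phases, so the first follow-up visit is either the same time point as the end of treatment or three months after it.

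**Working it through.** **Step 1: are the marks really in the follow-up columns?** Table 2 has seven visit columns: baseline, treatment months 1, 2, 3, and follow-up months 3, 6, 12. Counting marks per row:

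| Row type | Baseline | Treatment 1, 2, 3 | Follow-up 3, 6, 12 | Marks |
|---|---|---|---|---|
| Enrolment rows | 1 | 0 | 0 | 1 |
| Active pill; placebo | 0 | 3 | 3 | 6 |
| Adverse events | 0 | 3 | 3 | 6 |
| Lung function, CAT and other outcomes | 1 | 3 | 3 | 7 |

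The intervention rows follow the same pattern as the adverse event row, and the outcome rows fill every column. The columns therefore align, and the marks are not a product of text extraction.

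**Step 2: text against table.**

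| Place | Study treatment after week 12? |
|---|---|
| Abstract; section 2.1; section 2.5.1 (both arms) | No, 12 weeks |
| Section 2.6.3; introduction to Table 2 | A post-treatment period is presupposed |
| Table 2 phase headings | Treatment phase of 3 months, then follow-up |
| Table 2 intervention rows | Marked at every follow-up visit |

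**Step 3: visit times under each origin.** In months from randomisation:

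- Follow-up counted from randomisation: 0, 1, 2, 3, 3, 6, 12. Month 3 appears twice and the last visit is at month 12.
- Follow-up counted from end of treatment (month 3): 0, 1, 2, 3, 6, 9, 15. The last visit is at month 15.

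Neither set is monthly in the follow-up phase, although the heading says so.

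**Step 4: size of the discrepancy.** The inputs come from section 2.5.1: 10 pills three times daily, 0.19 g per pill. They serve only to size the gap. The assumption is daily dosing without a break up to the last marked visit.

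- Pills per day: 10 × 3 = 30.
- Text, 12 weeks: 12 × 7 = 84 days; 30 × 84 = 2,520 pills; 2,520 × 0.19 = 478.8 g.
- Table, origin at randomisation: 365 days; 30 × 365 = 10,950 pills; × 0.19 = 2,080.5 g; 365 / 84 = 4.35 times.
- Table, origin at end of treatment: 15 months = 1.25 × 365.25 ≈ 457 days; 30 × 457 = 13,710 pills; × 0.19 = 2,604.9 g; 457 / 84 = 5.44 times.

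**Step 5: consequence for the decline endpoint.** Under the text, the share of the observation window spent on the study pill is 84 / 365 = 23% (last visit at month 12) or 84 / 457 = 18% (last visit at month 15). Under the table read literally it is 100%. On and off treatment here refer to the study pill or placebo only; section 2.5.2 gives both arms background anti-tuberculosis therapy for 8 + 16 = 24 weeks.

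**The case against.** The best defence is that the text leaves little doubt. It states 12 weeks four times, once for each arm and twice for the trial. Sections 2.6.3 and 2.7 assume a post-treatment phase, and Table 2 itself labels the later columns as follow-up. On that view the six extra marks are a slip in two table rows. This is plausible, and it rules out a stronger reading: a reader might infer that treatment duration is undefined. It is not undefined. It is stated consistently in the text and contradicted in the table. The defence does not remove the contradiction, because nothing in the article says that the marks are an error or gives them another meaning.

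A second objection also stands in part. The 4.3- to 5.4-fold figure needs continuous dosing between visits, and no regimen after week 12 is described. The figure is the literal-reading extreme.

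Other inferences are tempting but unsupported:

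- *Sites might diverge in what they give.* Section 2.2 names one recruiting hospital.
- *Consent and drug supply would differ several-fold.* No supply plan is shown, and consent pages are not among the material available.
- *Adverse event contacts in the first 12 weeks would be 12 or 3.* The abstract says "Systematic safety surveillance will be performed through weekly monitoring of adverse events", while Table 2 has monthly columns. Section 2.6.3 adds real-time self-report. Weekly surveillance between monthly visits is compatible with all three, and the article does not say that the visit columns are the only contacts. The wording needs aligning, but this is a minor clarification.

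**Conclusion.** The point holds as an internal contradiction. The active and placebo rows of Table 2 show study medication at all three follow-up visits, against 12 weeks in the abstract and sections 2.1 and 2.5.1 and against the post-treatment phase assumed in sections 2.6.3 and 2.7. Because both statements are printed in the article, this is not detail left to a fuller document.

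If the marks mean uninterrupted dosing, exposure is about 4.3 times the 12-week course with follow-up counted from randomisation and about 5.4 times with follow-up counted from end of treatment. If they are a slip, exposure is unchanged and only the table is wrong. The documents do not settle which applies. Either way, the primary endpoint of 12-month decline needs to be declared an on-treatment or a largely off-treatment comparison, and its visits need a stated time origin. The mismatch between the monthly heading and the 3-, 6- and 12-month columns is a smaller fault in the same table.

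**What to change.** 1. Reconcile the active and placebo rows of Table 2 with the abstract and sections 2.1 and 2.5.1 so that all give one treatment duration. The sponsor must decide which is right.
2. State in Table 2 whether follow-up months count from randomisation or from end of treatment, and make the follow-up heading agree with the columns.
3. In section 2.6.1.2, and wherever else follow-up visits supply an endpoint, label the comparison as on- or off-treatment to match.
4. As a minor clarification, make the adverse event wording in the abstract and Table 2 agree, for example by saying how weekly surveillance relates to the monthly visits.

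The cost is a correction to the table and a few sentences, notified to study staff and the ethics committee. The change itself needs no new visits or measurements.

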### 2.8 Data analysis

Two researchers independently entered observational data to establish a standardized database, with subsequent statistical analyses performed using SPSS 25.0. Quantitative variables exhibiting normal or approximately normal distributions are expressed as mean ± standard deviation (x̄±s). Between-group comparisons of means were analyzed via independent t-tests, while within-group longitudinal changes were assessed using paired t-tests. Categorical data were evaluated through χ^2^ tests or Wilcoxon rank-sum tests, and ordinal data were analyzed using non-parametric methods (e.g., Kruskal-Wallis test for multi-group comparisons). All statistical inferences employed two-tailed tests with a predefined significance threshold of α = 0.05.

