### 2.4 Sample size estimation, blind and randomization

Sample size determination was conducted using methodology derived from prior RCT, indicating a minimum requirement of 31 participants per group. This calculation yields a baseline enrollment target of 62 subjects. To account for potential attrition (anticipated dropout rate = 20%) and ensure adequate power for intent-to-treat analysis, the final adjusted sample size was established at 74 participants.

This randomized controlled trial will enroll 74 participants allocated through SAS-generated block randomization with 1:1 assignment to either the intervention or control arm. Opaque sequentially numbered envelopes containing allocation codes will be managed by a head nurse. The head nurse on duty distributes the envelopes to the attending physicians according to the order of subjects’ enrollment, and the attending physicians assign the treatment plans to the patients according to the group numbers. The head nurse on duty assigns a sequence number based on the attending physician’s diagnosis. A designated person from the project team is responsible for distributing the treatment medication to the subjects. A specific person within the research team enters the data, and a teacher from the statistical consulting room is responsible for data analysis. When the results are ready, a third party is present to jointly unblind the results. In accordance with the principles of blinding, neither the patients, the attending physicians, nor the data statisticians and analysts are aware of the specific group assignments.

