#### 2.5.2 Conventional treatment

Both treatment and control groups receive standardized anti-tuberculosis therapy following the WHO-recommended RIPE regimen—an intensive 8-week phase with daily rifampicin, isoniazid, pyrazinamide, and ethambutol, followed by a 16-week continuation phase with rifampicin and isoniazid—and concurrently receive guideline-concordant COPD management, including maintenance bronchodilator therapy.

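### Section 2.8 fixes unadjusted between-arm t-tests and within-arm paired t-tests not labelled descriptive, although baseline and repeated measures are collected: the cost is precision, and the paired tests cannot show a drug effect

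*Protocol article*

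**What the plan says.** Section 2.8 of the protocol article sets out the tests: "Between-group comparisons of means were analyzed via independent t-tests, while within-group longitudinal changes were assessed using paired t-tests". Categorical and ordinal data go to χ² or rank methods. One significance rule covers everything: "All statistical inferences employed two-tailed tests with a predefined significance threshold of α = 0.05".

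The section does not say whether the between-arm t-test is on follow-up values or on change from baseline, nor at which visit. It names no ANCOVA, mixed model or other baseline adjustment. It does not say that the between-arm comparison alone carries the efficacy conclusion.

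Three other places bear on this:

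- **Table 2 (section 2.7)** marks FVC, FVC%, FEV1%, FEV1/FVC, CAT and the TCM symptom score at baseline and in six later columns: months 1, 2 and 3 of treatment, then months 3, 6 and 12 of follow-up.
- **Section 2.6.1.2** makes long-term decline, from serial spirometry, part of the primary outcome.
- **Section 2.5.2** gives active therapy to everyone: "Both treatment and control groups receive standardized anti-tuberculosis therapy following the WHO-recommended RIPE regimen". COPD management with maintenance bronchodilators is added in both arms.

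**The concern.** Two features of the stated analysis fit the design poorly.

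First, each continuous outcome has a baseline value, which usually predicts the later value. A comparison that leaves it out carries variance that could be removed at no cost. With a target of 31 evaluable patients per arm, that matters.

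Second, the only method assigned to longitudinal change is a paired test inside each arm. Section 2.3.1 requires no anti-tuberculosis drugs in the past month, and the Introduction describes the patients as treatment-naive. Both arms therefore start effective background treatment at about the time of the baseline measurement, and improvement on placebo is plausible. A significant before-after change in the active arm then mixes background therapy, natural course and any drug effect. Significance in one arm and not in the other is not a comparison of the arms. Because all tests share one threshold and none is called descriptive, nothing in the text stops a paired p-value from being read as evidence for the pill.

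**Working it through.** **Inputs from the documents.** Section 2.4 gives the planned evaluable number ("indicating a minimum requirement of 31 participants per group") and 1:1 allocation. Section 2.8 gives two-sided α = 0.05.

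**Inputs not given, so assumed.** Power is taken as 80%. The correlation *r* between baseline and follow-up is shown from 0.3 to 0.8. The protocol states no effect size, SD or power, so the figure of 31 cannot be reproduced forward; it can only be solved backward.

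**Step 1: implied effect.** With the normal approximation, d = (1.960 + 0.842) × √(2/31) = 0.712 SD. With the exact t distribution it is 0.723. The power figures below agree under either version to the precision shown.

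**Step 2: power at the same n and the same effect.** At d, the standardised test statistic has mean 1.960 + 0.842 = 2.802.

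- ANCOVA multiplies the SD by √(1 − r²), so power = Φ(2.802/√(1 − r²) − 1.960).
- A t-test on change multiplies the SD by √(2(1 − r)), so power = Φ(2.802/√(2(1 − r)) − 1.960).

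| r | t-test on follow-up value | t-test on change | ANCOVA | Variance removed by ANCOVA (r²) |
|---|---|---|---|---|
| 0.3 | 80% | 66% | 84% | 9% |
| 0.5 | 80% | 80% | 90% | 25% |
| 0.7 | 80% | 95% | 97.5% | 49% |
| 0.8 | 80% | 99% | 99.7% | 64% |

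Example at r = 0.5: 2.802/0.866 − 1.960 = 1.275, and Φ(1.275) = 0.899.

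ANCOVA is never worse than either t-test in the table. How much it gains depends on *r* and on which t-test is meant, and the document settles neither.

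**Step 3: paired tests when the drug does nothing.** Suppose both arms improve by 0.3 SD of the outcome, with r = 0.7 and n = 31.

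- The standardised mean change is 0.3/√(2 × 0.3) = 0.387.
- The power of the paired t-test in each arm is 0.551.
- The chance that active is significant and placebo is not is 0.551 × (1 − 0.551) = 0.247, about 25%.
- The comparable error of the between-arm test, a false result favouring active, is 0.05/2 = 2.5%.

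The product p(1 − p) cannot exceed 0.25, so this scenario is close to the worst case. At a common improvement of 0.5 SD, the standardised change is 0.5/√0.6 = 0.645 and the paired test has power 0.935. The one-sided pattern then falls to 0.935 × 0.065 = 6%, but the active arm alone is significant in about 94% of trials with no drug effect.

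**The case against.** The strongest defence is that the independent t-test is a valid comparison of randomised arms. Its type I error is 5% per test, and its standard error already allows for chance baseline imbalance. That stands: the cost is precision, not bias.

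Four stronger readings are tempting, and the text does not support them:

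- **That paired tests are the efficacy test.** Section 2.8 assigns comparisons between groups to the independent t-test and uses paired tests for change within groups. Misuse in reporting is a risk left open, not something planned.
- **That baseline is certainly ignored.** The t-test could be on change. If so, the loss against ANCOVA is about 2.5 percentage points at r = 0.7 and under 1 point at r = 0.8, though 10 points at r = 0.5 and 18 at r = 0.3.
- **That the repeated structure is wholly unused.** Section 2.6.1.2 quantifies annual decline from at least three tests per patient over 12 months. A between-arm t-test on that per-patient summary would be legitimate. TDI is itself a change measure.
- **That patients drop out of the analysis visit by visit.** The article does not say how missing values are handled, and a protocol article may leave that to the analysis plan.

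What the defence does not answer is that the article names its tests outright, includes no baseline-adjusted comparison, and puts paired p-values on the same footing as between-arm ones.

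**Conclusion.** The point holds as a matter of precision and interpretation. The planned between-arm test is valid but less precise than the collected data allow, and the paired tests cannot show a drug effect in a trial where both arms receive active background therapy.

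The size is conditional. The gain from baseline adjustment runs from small (80% to 84% at r = 0.3, against a follow-up-value t-test) to large (80% to 97.5% at r = 0.7). At high correlation it is slight if the t-test is on change. These figures assume 80% power at 31 per arm and a correlation that the protocol does not give. The 25% for a misleading within-arm pattern is near the maximum possible and depends on how far both arms improve. It would become a false claim only if the authors drew one from paired p-values, which the text neither plans nor rules out.

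**What to change.** Set the between-arm analysis by type of outcome and state it in section 2.8 before unblinding:

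- **Continuous outcomes with a baseline value (FVC, FVC%, FEV1%, FEV1/FVC, CAT, TCM score):** a between-arm ANCOVA at one stated time point, adjusted for the baseline value. Alternatively, a mixed model for repeated measures with baseline, treatment, visit and treatment-by-visit. Report the adjusted difference with its 95% confidence interval.
- **Annual FEV1 decline:** compare arms by a mixed slope model (treatment-by-time) or by per-patient slopes. ANCOVA at a single visit does not answer this question.
- **TDI:** compare between arms with adjustment for BDI, since TDI has no baseline value of its own.
- **mMRC:** keep an ordinal between-arm method.
- **Within-arm paired results:** label them descriptive and draw no efficacy claim from their p-values.

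The measurements are already in Table 2, and SPSS 25.0, already named, can fit these models. The cost is revised wording, a decision on the primary time point, and slightly more analysis work because one model does not serve every outcome.
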